## Quality control

5

### Data management system

5.1

This study will prospectively recruit patients, with recruitment anticipated to conclude in 2028. Data will be stored in the Perinatal Cloud Database, a platform accessible via both desktop and mobile devices. Each participating center and patient will be assigned a unique identification number. The online platform ensures secure data storage, facilitates data export based on specified search criteria, and incorporates a logical validation system that flags missing data, outliers, and inconsistencies. This system is designed to uphold data reliability, integrity, and accuracy, while supporting audit trails, data management, and source data validation. As participating centers utilize heterogeneous Electronic Health Record (EHR) systems, data are manually abstracted by trained research coordinators and entered into the central online Case Report Form (CRF). To ensure data fidelity, this process is supported by a rigorous, multi-tiered quality control and data validation protocol designed specifically to mitigate errors associated with manual entry.

### Personnel training

5.2

Prior to the implementation of the electronic data capture system, comprehensive training will be conducted to ensure all personnel are adequately prepared. Upon completion of training, access rights to the corresponding system will be granted to relevant personnel.

### Verification by regulatory authorities

5.3

A three-tiered quality control process has been established to ensure the accuracy of data entry at each hospital. Each hospital is required to designate a primary data quality controller to review all data entries. Additionally, the coordination center will appoint secondary data quality controllers at each hospital, who will sample and inspect a minimum of 30% of the data entries on a weekly basis. The Data Committee represents the third level of quality control, performing monthly reviews of at least 10% of the data entries.

To further enhance diagnostic consistency and minimize misclassification bias across centers, a central adjudication committee will be established. This committee, composed of at least two expert neonatologists blinded to the originating site, will independently review a random sample of 10% of all enrolled cases, as well as all ambiguous cases flagged by site investigators. This review ensures the uniform application of the Montreux criteria, particularly regarding radiographic interpretation and the exclusion of other etiologies. Furthermore, WeChat groups have been established at each hospital to provide real-time feedback on inspection results and facilitate necessary corrections.

### Archiving of traceable raw data

5.4

Source-verified, anonymized copies of essential medical records will be securely archived digitally at the coordinating center. To ensure data security and redundancy, three separate backup copies will be maintained. Site-level investigators will have access only to their own center's data. The central data management committee will have monitored access to the complete dataset for quality control and unified statistical analysis.

## Statistical analysis

6

### Statistical analysis plan

6.1

Continuous variables will be summarized as mean ± standard deviation (SD) or median with interquartile range (IQR), depending on distribution. Categorical variables will be presented as frequencies and percentages. Group comparisons will be conducted using the student's *t*-test or Mann–Whitney *U* test for continuous variables, and the *χ*² test or Fisher's exact test for categorical variables.

Univariate logistic regression will be used to examine associations between NARDS and study outcomes. Multivariable logistic regression will then be performed to identify independent predictors. Missing data will be addressed primarily using multiple imputation by chained equations (MICE), assuming data are missing at random. Variables with excessive missingness will be excluded according to predefined thresholds, and the imputation model will be structured accordingly. Sensitivity analyses will include complete-case analysis, k-nearest neighbors (k-NN) imputation, and inverse probability weighting to evaluate the robustness of findings to loss to follow-up. A two-sided *p* < 0.05 will be considered statistically significant. All analyses and visualizations will be conducted using R software (version 4.3.3).

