### Recruitment, enrollment, and termination

3.5

Recruitment for the SZ-NARDS cohort study will commence on January 1, 2025, at nine hospitals in Shenzhen, Guangdong Province, China. Enrollment and follow-up will be conducted concurrently, with recruitment continuing until the target sample size is achieved. The cohort will be considered complete once all participants have finished the 3-year follow-up period. Research coordinators will provide eligible parents with a detailed study pamphlet and will conduct face-to-face introductions to the cohort. A flowchart of the enrollment process is presented in Figure 2. A participant's active involvement in the study will cease upon death, guardian withdrawal of consent, or confirmed transfer to a non-participating medical facility where follow-up is not feasible.

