Post-Discharge Follow-Up (Up to 36 months)	For deceased infants: date and primary cause of death For survivors: occurrence of major complications (e.g., severe neurodevelopmental impairment, chronic respiratory morbidity, growth restriction) For lost cases: date and reason for loss to follow-up

aEEG, amplitude integrated electroencephalogram; ARDS, acute respiratory distress syndrome; CRP, C-reactive protein; CT, computed tomography; ECMO, extracorporeal membrane oxygenation; HFOV, high-frequency oscillatory ventilation; MRI, magnetic resonance imaging; OI, oxygenation index; PBMC, peripheral blood mononuclear cells; PCT, procalcitonin.

a Wechat (Tencent Inc., Shenzhen, China) is a widely used social communication application in China, functionally similar to WhatsApp.

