While innovative, our study has limitations. A primary limitation is the potential for significant selection bias, as the study is confined to Shenzhen, a single, economically developed “special economic zone” in China. The healthcare resources, patient demographics, and socioeconomic status in this region are not representative of the broader diversity across China, including rural or less developed areas. This may result in a study cohort with better outcomes than the national average, and therefore, our findings must be interpreted with caution and require validation in more geographically and socioeconomically diverse populations before they can be generalized. Loss to follow-up is another concern in longitudinal work. We have instituted multiple strategies to minimize dropout and will address any residual missing data with modern statistical methods like multiple imputation and inverse probability weighting, accompanied by sensitivity analyses. While the multicenter nature of the study introduces heterogeneity in clinical management, this is also a methodological opportunity. By meticulously documenting variations in interventions (e.g., ventilation strategies, surfactant use), we can leverage advanced statistical methods, such as propensity score matching or inverse probability weighting, to conduct comparative effectiveness analyses in a real-world setting. This can generate valuable hypotheses for future randomized controlled trials.

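### The sensitivity analyses listed for loss to follow-up all rest on missing at random or something stronger, so their agreement cannot show robustness of the 36-month results to informative loss

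*Protocol article*

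**What the plan says.** Section 6.1 (Statistical analysis plan) fixes the main method and its assumption: "Missing data will be addressed primarily using multiple imputation by chained equations (MICE), assuming data are missing at random". It then names the checks: "Sensitivity analyses will include complete-case analysis, k-nearest neighbors (k-NN) imputation, and inverse probability weighting". The same sentence gives the purpose: "inverse probability weighting to evaluate the robustness of findings to loss to follow-up". The Discussion (section 7) calls loss to follow-up a concern and answers it with "modern statistical methods like multiple imputation and inverse probability weighting, accompanied by sensitivity analyses", without saying which further analyses are meant.

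On how children are lost, section 3.5 ends active participation on death, "guardian withdrawal of consent, or confirmed transfer to a non-participating medical facility where follow-up is not feasible". Table 1 provides for the recording of the circumstances: "For lost cases: date and reason for loss to follow-up". Section 4.2 makes survival at 36 months corrected age the primary follow-up outcome. NDI is a secondary outcome there, as are the loss rates at 24 and 36 months. No section names an analysis that departs from MAR, and no stated analysis uses the recorded reason for loss.

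**The concern.** A sensitivity analysis for missing data is useful to the extent that it varies the assumption in doubt. Here that assumption is that, given what was measured, lost children fare like those followed. Withdrawal by a guardian, a transfer that makes follow-up infeasible, and non-return over three years can each depend on how the child is doing, in either direction. The listed methods mainly vary the technique and leave that assumption in place.

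The risk is one of reporting. If the methods give similar answers, the paper may present this as robustness to loss to follow-up, although it is silent on informative loss. Long-term survival and NDI are among the results that the article says earlier cohorts did not provide.

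**Working it through.** **Step 1. What each method needs when the 36-month outcome is missing and a rate is estimated.**

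| Method | Role in section 6.1 | Condition for an unbiased rate |
|---|---|---|
| MICE | Main | Loss independent of the unseen outcome given observed data (MAR) |
| k-NN imputation | Sensitivity | The same, with a non-parametric outcome model |
| Inverse probability weighting | Sensitivity | The same, modelling loss instead of outcome |
| Complete case | Sensitivity | Loss unrelated to the outcome altogether (stronger) |

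No row allows loss to depend on the outcome after conditioning on observed data.

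**Step 2. Inputs.** The article's only sample-size figure reproduces: 10 events × 10 predictors = 100 deaths; 100 / 0.126 = 793.65, rounded up to 794, raised to a target of 1,000. The present point does not depend on it. It supplies the number of hospital survivors: 1,000 × (1 − 0.126) = 874. The following are assumptions, because the article gives no values: loss of 10% to 30%, NDI of 25% in those followed, and an odds ratio (OR) for NDI, lost versus followed, of 0.5 to 3.

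**Step 3. Size for NDI.** Odds in those followed are 0.25 / 0.75 = 1/3. In lost children, OR 2 gives odds of 2/3, a rate of 40%. OR 3 gives odds of 1, a rate of 50%. OR 0.5 gives odds of 1/6, a rate of 14.3%. The true rate is (1 − loss) × 25% + loss × rate in lost children. The half-width is 1.96 × √(0.25 × 0.75 / n), with n = 874 × (1 − loss).

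| Loss | n followed | 95% half-width | OR 0.5 | OR 2 | OR 3 |
|---|---|---|---|---|---|
| 10% | 787 | 3.0 points | 23.9% | 26.5% | 27.5% |
| 20% | 699 | 3.2 points | 22.9% | 28.0% | 30.0% |
| 30% | 612 | 3.4 points | 21.8% | 29.5% | 32.5% |

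Example at 20% loss, OR 2: 0.8 × 25 + 0.2 × 40 = 28.0%. The bias for OR 2 to 3 is 1.5 to 2.5 points at 10% loss, 3.0 to 5.0 at 20% and 4.5 to 7.5 at 30%. At 20% loss and OR 2 it is slightly below the half-width (3.0 against 3.2).

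**Step 4. Do the listed methods reveal it?** A simulation used 400 runs of 874 children, one observed covariate related to both outcome and loss, and a binary outcome.

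| Odds of loss multiplied by the outcome | Loss | True | Multiple imputation | k-NN | Weighting | Complete case |
|---|---|---|---|---|---|---|
| × 1 (MAR) | 17.5% | 29.2% | 29.3% | 29.2% | 29.3% | 28.2% |
| × 2 | 21.4% | 29.3% | 26.2% | 26.1% | 26.2% | 24.8% |
| × 3 | 24.1% | 29.4% | 23.7% | 23.6% | 23.7% | 22.1% |

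Under informative loss, multiple imputation, k-NN and weighting agree within 0.1 point while lying about 3 to 6 points below the truth. Complete case differs from them by 1.4 to 1.6 points and is further off. Its gap under MAR is already 1.1 points (29.3 − 28.2), so a gap mainly reflects measured predictors of loss and does not identify informative loss.

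**Step 5. Survival.** Counting every lost child as alive, then every lost child as dead, gives bounds whose width equals the fraction with unknown status: 10 points at 10% unknown, 20 points at 20%.

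**The case against.** There is a fair case on the other side.

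- The article is condensed, its list of sensitivity analyses is not worded as exhaustive, and section 6.6 refers to an approved analysis plan that is not shown. That plan may contain a departure from MAR. This limits the point to the methods listed, but does not make those methods suited to informative loss.
- The purpose clause may attach to inverse probability weighting alone. The conclusion is the same on either reading, since weighting needs MAR too.
- A reader might infer that the listed analyses are redundant and that k-NN should be dropped. The documents do not support that. k-NN relaxes the parametric form of MICE, weighting models loss instead of outcome, and complete case shows how far measured variables predict loss. These are legitimate checks of a different question.
- Measured data may explain much of the loss. The study records socioeconomic status, parental education, severity scores and comorbidities, has visits at 6, 12, 18 and 24 months, and gives the Bayley scales at 24 as well as 36 months. A child lost only at the last visit may have a 24-month score. Coordinators, reminders and travel subsidies (section 3.8.3.1) should reduce loss, and telephone contact (Figure 1 legend) makes survival status easier to obtain than NDI. All this makes MAR more credible, but does not test it.
- For associations, complete-case odds ratios from logistic regression can survive loss that depends on the outcome but not on outcome and predictor jointly. That special case does not protect the survival and NDI rates.

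**Conclusion.** The point holds in a limited form. For missing follow-up outcomes, the main analysis and all three listed sensitivity analyses need MAR or more. Their agreement should therefore not be reported as robustness to informative loss. In the central illustration the effect on NDI is about as large as sampling error or somewhat larger. At 10% loss it is below sampling error; at 30% it exceeds it.

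These sizes rest on assumed loss, NDI rates and odds ratios, and suppose that measured variables do not explain the difference. They concern NDI; for survival only the bounds are given. A reader might go further and infer that the long-term rates will be biased, or that the article claims robustness to unmeasured informative loss. Neither follows: the article states MAR openly, gives no loss rate, and says nothing on the direction or strength of informative loss.

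**What to change.** Keep the listed analyses, describe them as checks of model form and of measured predictors of loss, and add to section 6.1:

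- a delta-adjusted (tipping-point) version of the planned MICE for 36-month survival and for NDI, shifting the odds in lost children over a prespecified range, for example 0.5 to 3;
- separate shifts by the recorded reason for loss (withdrawal, transfer, not contactable) where numbers allow;
- best- and worst-case bounds for survival;
- a report of the shift at which the conclusion changes.

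Include the 24-month scores and earlier visits in the imputation model, so that the shift covers only what remains unexplained. State also that exclusion criterion 4 in section 3.6.1, on unavailable outcome data, does not remove children lost after discharge; otherwise they would leave the data set before any imputation or weighting.

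The cost is a few sentences and a few more runs of a model already planned, with no new data. The downside is a wider reported range for the long-term rates.

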### Machine learning and predictive modeling

6.2

Beyond conventional regression, predictive modeling will employ a suite of algorithms, including penalized logistic regression (Elastic Net), decision trees, random forests, gradient boosting machines, support vector machines, and artificial neural networks. Two primary prediction tasks will be addressed: Early identification of neonates at risk of severe NARDS (OI > 16 within 72 h of diagnosis); Long-term prognosis (mortality, NDI, SRM, or growth restriction at the 24- and 36-month corrected age). Candidate predictors will be selected based on clinical relevance and temporal availability (within 24 h for early warning models; within 7 days for prognostic models). Feature selection and regularization will primarily use Elastic Net. To identify novel NARDS endotypes, Integrative Multi-Omics Factor Analysis (MOFA) or similar unsupervised data integration approaches [e.g., sparse Partial Least Squares Discriminant Analysis (sPLS-DA)] will be employed to identify latent factors and co-varying molecular pathways across omics layers. These integrated molecular signatures will subsequently serve as input features for downstream machine learning models (e.g., Random Forest) to construct highly discriminative and biologically informed predictive classifiers.

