**Results:**

The primary objective of this study is to characterize the epidemiology of NARDS in this regional population and to test the following hypotheses: (1) The true incidence, etiology, and mortality rates of NARDS in Shenzhen will differ from existing international and Chinese cohorts, and these differences can be systematically explained by specific clinical and demographic factors. A multi-modal predictive model that integrates early clinical variables with multi-omics biomarkers has the potential to accurately identify neonates at high risk for severe NARDS [oxygenation index (OI) ≥ 16] and long-term adverse outcomes [Area Under the Receiver Operating Characteristic Curve (AUROC) > 0.85].

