#### Inclusion and exclusion criteria

3.6.1

Neonates will be enrolled consecutively upon meeting the full set of Montreux criteria for the diagnosis of NARDS during hospitalization. This cohort will include infants of all gestational ages, including premature infants, provided their respiratory distress meets all five Montreux criteria. These criteria include: (1) an acute onset of symptoms within one week following a known or suspected clinical insult; (2) exclusion of respiratory distress attributable to neonatal respiratory distress syndrome (NRDS), transient tachypnoea of the newborn (TTN), or congenital anomalies; (3) radiological evidence of bilateral, diffuse irregularities, including reduced translucency or opacities, that cannot be explained by conditions such as pleural effusion, atelectasis, NRDS, TTN, or congenital anomalies; (4) absence of congenital heart disease as the cause of pulmonary oedema, with echocardiographic confirmation required to verify the origin of the oedema; and (5) the presence of an oxygenation deficit, categorized by the OI as mild (4 ≤ OI < 8), moderate (8 ≤ OI < 16), or severe (OI ≥ 16). All five criteria must be fulfilled for diagnosis.

Exclusion criteria include: (1) respiratory distress due to primary surfactant deficiency (e.g., hyaline membrane disease), TTN, or congenital lung malformations; (2) congenital heart disease resulting in pulmonary oedema; (3) known genetic syndromes or chromosomal abnormalities; (4) data that did not conform to the Montreux criteria or cases with unavailable outcome data; and (5) abandonment or death occurring within 24 h of birth.

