### Data collection

3.8

All data variables for the study are summarized in Table 1, with the study timeline illustrated in Figure 3.

**Table 1 T1:** Details of measurements in the SZ-NARDS cohort study.

Phrase	Measurements
NICU Characteristics	Bed capacity, annual NICU admissions, availability of cardiac surgery, presence of in-house ICU physicians, ICU fellowship training programs, trauma care services, ECMO capabilities, high-frequency oscillatory ventilation (HFOV), respiratory therapists, burn care services, and point-of-care blood gas analysis.
Demographic data	
Guardian Information Perinatal information Neonatal characteristics	Age, gender, ethnicity, identification number, phone number, WeChat^a^ contact, home address, marital status, socioeconomic status, and educational attainment.
	Gravidity, parity, type of pregnancy, gestational weight gain, pre-existing maternal conditions, pregnancy-related complications, and treatments received.
	Gestational age, birth weight, gender, mode of delivery, multiple birth status, Apgar score, birth hospital, transport method, transfer duration, umbilical artery blood gas results, and admission temperature.
Baseline (day 1)	Physical examination Neonatal illness severity scores: SNAP-II, SNAPPE-II, NCIS Comorbidities: bacterial infection, systemic inflammatory response syndrome (SIRS), sepsis, severe sepsis, septic shock Laboratory tests: umbilical artery blood gas, complete blood count, CRP, PCT, standard blood gas analysis, lactate, liver and renal function tests, electrolytes, lipids, glucose, coagulation profile Microbiological cultures: blood, midstream urine (if urinary tract infection suspected), stool, sputum, and optional tracheal aspirate Imaging: chest x-ray, lung ultrasound, cranial ultrasound, echocardiography, and non-invasive cardiac function assessments Ventilation and treatment data: respiratory support parameters and pharmacologic interventions Biological specimens for DNA analysis: plasma (1–1.5 ml; from peripheral/cord blood), urine (1–1.5 ml), stool, sputum, breast milk, and optional tracheal aspirate (all stored at –80°C)
In-Hospital Follow-Up (At the most critical phase, Day 28, and within 24 h before death or ECMO initiation)	Identical to baseline measurements: physical examination, illness severity scores (SNAP-II, SNAPPE-II, NCIS), comorbidities, laboratory tests, microbiological cultures, imaging, ventilation/treatment data, and biological specimens.

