#### Clinical data and key variable definitions

3.8.1

Demographic characteristics, baseline information, and follow-up data will be systematically recorded following admission and discharge. During hospitalization, data collected will include physical examination findings, neonatal critical illness scores, diagnoses, complications, biochemical parameters, pathogen cultures, imaging results, and treatments administered. Post-hospitalization follow-up assessments will be conducted at designated time points: on day 1 (within 24 h of NARDS diagnosis), during the acute exacerbation phase (defined as the moment when the OI reaches its peak), and on day 28 (or the final day of hospitalization if shorter than 28 days). For patients who succumb to their condition or require ECMO, data will also be gathered 24 h prior to death or the initiation of ECMO. Supplementary data, including hospitalization duration and associated costs, will also be documented.

Key clinical variables were standardized to ensure consistency in reporting:

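### The 7-day long-term prognostic models include mortality but are not restricted to infants alive at day 7, so predictor and outcome windows can overlap for early deaths

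*Protocol article*

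**What the plan says.** Section 6.2 of the protocol article names two prediction tasks. The second is "Long-term prognosis (mortality, NDI, SRM, or growth restriction at the 24- and 36-month corrected age"). Candidate predictors are chosen for clinical relevance and for when they become available: "within 24 h for early warning models; within 7 days for prognostic models". The section does not say whether the 7 days run from birth or from diagnosis, which infants are at risk, or when the mortality clock starts.

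Three other places bear on this:

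- **Who stays in the cohort (3.6.1).** The only exclusion for early death is "abandonment or death occurring within 24 h of birth". Later deaths in the first week remain.
- **What is recorded and when (3.8.1 and Table 1).** After day 1 the in-hospital sets are taken "At the most critical phase, Day 28, and within 24 h before death or ECMO initiation". The critical phase is "defined as the moment when the OI reaches its peak". For infants who die or need ECMO, "data will also be gathered 24 h prior to death or the initiation of ECMO". Table 1 makes each of these a repeat of baseline, including severity scores, laboratory tests, "ventilation/treatment data, and biological specimens". If the stay is shorter than 28 days, the day-28 set moves to the final hospital day.
- **The performance target (Abstract, Results).** The hypothesis covers severe NARDS and "long-term adverse outcomes [Area Under the Receiver Operating Characteristic Curve (AUROC) > 0.85".

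Section 6.3 validates by a random 70/30 split, cross-validation and bootstrap, with temporal or centre-level validation where feasible.

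**The concern.** A prognostic model needs a time at which the prediction is made. Predictors must be known by then, and the outcome must lie after it. A 7-day predictor window implies a prediction made at day 7. As written, an infant who dies on day 4 can still enter as an event, with predictors taken up to the point of death.

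The recording schedule sharpens this. For that infant the pre-death set falls on days 3–4, inside the window, while an infant who survives without ECMO never has such a set. Terminal values, or the bare existence of the record, would then carry the outcome into the predictors.

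At stake is whether the reported AUROC and calibration apply where the model would be used. A clinician applying it at day 7 has no infants left who died earlier in the week. The planned validation would not reveal the problem, because every held-out set is built from the same records under the same schedule. The AUROC target in the Abstract also extends to long-term outcomes, so the overlap could influence whether that hypothesis appears to be met.

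**Working it through.** **1. Do the windows overlap on the text?**

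| Element | Where | What is fixed |
|---|---|---|
| Predictor window | 6.2 | up to 7 days, day zero unnamed |
| Outcome | 6.2 | includes mortality, clock start unnamed |
| Early deaths removed | 3.6.1 | only those within 24 h of birth |
| Event-triggered record | 3.8.1, Table 1 | only infants about to die or start ECMO |
| Bar on using that record | none found | – |

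Taken together, deaths between 24 h after birth and day 7 are allowed as events in a model whose predictors run to day 7.

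**2. The plan's own event figure.** Section 3.6.2 requires 10 events × 10 predictors = 100 deaths at 12.6% mortality: 100 / 0.126 = 793.7, so 794, as stated. At the target of 1,000 infants, 1,000 × 0.126 = 126 in-hospital deaths are expected. That calculation serves an in-hospital mortality model; here it only supplies a count of deaths.

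**3. How large could the effect be?** The document gives neither the share f of deaths before day 7 nor any AUROC for early deaths. Everything in this step is assumption. Take a true AUROC of 0.75 and f = 20%, 40%, 60%.

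AUROC averages over death–survivor pairs, so for mortality alone it is the weighted mean of the values for early and later deaths:

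AUROC = f × A_early + (1 − f) × 0.75.

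- *(a) Early deaths ranked almost perfectly, A_early = 0.98.*
  - f = 20%: 0.196 + 0.600 = 0.796
  - f = 40%: 0.392 + 0.450 = 0.842
  - f = 60%: 0.588 + 0.300 = 0.888
- *(b) One normal marker whose terminal value is 1 SD worse in early deaths.* An AUROC of 0.75 corresponds to d = √2 × z(0.75) = 0.954. Then A_early = Φ((0.954 + 1)/√2) = 0.916, and the mixture gives 0.783, 0.817, 0.850.
- *(c) Existence of the pre-event record used as a feature, with 1% of survivors assumed to have one because of ECMO.* Let Δ = ln(f/0.01) − ln((1 − f)/0.99). Then AUROC = f[0.99 Φ((d² + Δ)/(d√2)) + 0.01 × 0.75] + (1 − f)[0.99 × 0.75 + 0.01 Φ((d² − Δ)/(d√2))], which gives 0.79, 0.84, 0.90.

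A simulation of 400,000 infants agrees: 0.785 / 0.817 / 0.849 for (b) and 0.794 / 0.846 / 0.895 for (c). Restricting it to infants alive at day 7 returns 0.75.

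**4. If the four outcomes form a composite.** Assume 20% of the 1,000 − 126 = 874 survivors have an adverse outcome: about 175 events, plus 126 deaths, about 301 in all. Using the value in (a):

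- f = 50%: 63/301 = 0.209, so 0.209 × 0.98 + 0.791 × 0.75 = 0.80
- f = 60%: 75.6/301 = 0.251, so 0.251 × 0.98 + 0.749 × 0.75 = 0.81

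**5. Events left after a day-7 landmark.** 126 × (1 − f) = 100.8, 75.6, 50.4. Enrolment needed for 100 later in-hospital deaths would be 100 / (0.126 × (1 − f)) = 993, 1,323 or 1,985.

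**The case against.** The best defence is that early deaths were never meant to be in this model. Section 4.2 lists survival at 36 months under post-discharge outcomes, 3.8.3 follows survivors and names the same four outcomes, and in-hospital death or ECMO is a separate outcome in 4.1. If the 6.2 outcome is post-discharge mortality only, early in-hospital deaths fall outside the risk set and the overlap disappears. Likewise, availability within 7 days may simply mean a prediction made at day 7, which implies infants alive then. Both readings are possible. Neither is written down, and each would require the restriction proposed here.

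A second defence is that risk sets are commonly left to the analysis plan. That is fair as to detail, but the article itself fixes both the predictor window and the outcome, and that pairing is unsafe as stated.

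Third, a reader might infer that the plan will feed pre-death records to the model. The documents do not support that: 6.2 proposes neither last values nor record presence as a feature. The rule in 6.1 dropping variables with excessive missingness could remove a separate pre-event variable, although not a last-value feature. Section 3.8.4 also keeps a full treatment record, so day 1–7 predictors need not come from event-triggered sets. This defence stands. Even so, ordinary day 2–7 data from infants who die that week leave the overlap in place.

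**Conclusion.** The point holds as a conditional one. Section 6.2 permits predictors and deaths to overlap before day 7, and nothing elsewhere prevents it. Unless only post-discharge deaths are meant, performance for mortality, or for a composite containing it, would be optimistic and the validation in 6.3 could not show it.

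The documents do not support saying that performance will be inflated by a known amount, or that the 0.85 target will be passed because of it. The range of about 0.78–0.90 for mortality rests wholly on an assumed true AUROC of 0.75, an assumed 20–60% of deaths before day 7, and assumed behaviour of terminal data. At 20% every scenario stays below 0.85. At 60% the terminal-value scenario only just reaches it; clearly passing it needs near-perfect ranking of early deaths or use of record presence. The composite illustration stays at 0.80–0.81 even with 50–60% early deaths.

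NDI, SRM and growth restriction analysed separately at 24 and 36 months require survival and are not affected. The 24 h early-warning model is outside this point.

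**What to change.** In 6.2:

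- Name day zero for the 24 h and 7-day windows.
- Fit and validate the 7-day prognostic models only in infants alive at the end of day 7, and count deaths only after it.
- Exclude the pre-death/pre-ECMO record, data and specimens, from the predictors of these models. The landmark alone is not quite enough: an infant who dies within 24 h after it has a pre-death set that can fall inside the window.
- Predict deaths before day 7 with the 24 h predictors only.
- If the outcome is meant as post-discharge mortality, say so and state the matching risk set.

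Data collection does not change. The cost is in events: of about 126 expected in-hospital deaths, about 101, 76 or 50 remain if 20%, 40% or 60% occur before day 7. The number of candidate predictors in the 7-day mortality model should be planned with that in mind. The reported AUROC is likely to be lower, but it will describe the infants for whom a day-7 prediction can be made.
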